### Transcranial direct current stimulation

The tDCS will be administered using a battery-powered direct current stimulator (Model MBM-IV400, manufactured by Jiangxi Huaheng Jingxing Medical Technology Co., Ltd., located in Jiangxi, China) through two saline-soaked sponge electrodes (3.5 cm × 3.5 cm). According to the International 10–20 system, the anodal electrodes will be positioned over the mPFC, on the sites corresponding Fpz, whereas the cathodal electrode will be placed above the visual cortex, corresponding to Oz. The current intensity is set at 2 mA, and the electrode area is 4cm by 5 cm. The tDCS stimulation will occur once a day, 5 days per week, for 4 consecutive weeks. For the active tDCS condition, each session will involve delivering a 2 mA direct current for 30 minutes, with ramp-up and ramp-down periods of 30 seconds each. For sham tDCS, the stimulation will utilize the same active tDCS arrangement, with an intensity of 2 mA. However, the current will be applied only for the 30 s ramp-up phase at the beginning and 30 s ramp-down phase at the end of the stimulation.

### Music therapy

For music selection, we will select western Mozart and Chinese classical music based on previous research (19, 30). For Western music, we will select Mozart’s Sonata K.448, a choice based on relevant literature that demonstrating its positive effects on improving symptoms in patients with schizophrenia (30). For traditional Chinese classical music, Pingsha Luoyan (Wild Geese Descending on the Sandbank), Chunjiang Huayueye (Moonlit River in Spring), Gaoshan Liushui (High Mountains and Flowing Water), and Shimian Maifu (Ambush from Ten Sides) will be selected according to a previous study by Lam et al. (19). For details, see **Table 2**. Participants in Group 1 (active tDCS combined with MT group), Group 2 (sham tDCS combined with MT group), and Group 4 (MT group) will engage in 20 sessions, each lasting 30 minutes, conducted once daily, five days per week over a four-week period. Notably, tDCS and MT will be conducted simultaneously in the Group 1 and Group 2. To minimize the potential confounding effects of temporal variables across the four groups (Groups 1, 2, 3, and 4), each treatment will be conducted within the same time period on the same day, with consistent start and end times. Participants in the control group (Group 5) will continue their regular medication treatment without receiving tDCS or MT. The detailed experimental design and operational procedures, please see to **Figure 2**.

**Table 2 T2:** The standardize arrangement for music intervention.

Session	Music Category	Music Title
1	Western Mozart	Mozart’s sonata K.448
2	Chinese classical music	Pingsha Luoyan
3	Western Mozart	Mozart’s sonata K.448
4	Chinese classical music	Chunjiang Huayue Ye
5	Western Mozart	Mozart’s sonata K.448
6	Chinese classical music	Gaoshan Liushui
7	Western Mozart	Mozart’s sonata K.448
8	Chinese classical music	Simian Maifu
9	Western Mozart	Mozart’s sonata K.448
10	Chinese classical music	Erquan Yingyue
11	Western Mozart	Mozart’s sonata K.448
12	Chinese classical music	Zuiyu Changwan
13	Western Mozart	Mozart’s sonata K.448
14	Chinese classical music	Youlan
15	Western Mozart	Mozart’s sonata K.448
16	Chinese classical music	Saishang Qu
17	Western Mozart	Mozart’s sonata K.448
18	Chinese classical music	Xiyang Xiaogu
19	Western Mozart	Mozart’s sonata K.448
20	Chinese classical music	Meihua Sannong

**Figure 2 f2:**
[figure not shown]
Study schedule for the participants in the randomized, double-blind, sham-controlled trial. fNIRS, Functional Near-Infrared Spectroscopy. MT, music therapy; tDCS, transcranial direct current stimulation.

### Outcomes

The study will utilize the Chinese version of the MATRICS Consensus Cognitive Battery (MCCB), which has demonstrated high efficacy in assessing cognitive function. To mitigate potential learning effects, various parallel versions of the MCCB will be employed at different assessment stages. Previous studies have demonstrated that the Chinese version of MCCB exhibits good test-retest reliability and validity, making it suitable for assessing cognitive dysfunction in patients with schizophrenia at each visit (31, 32). Cognitive function and psychotic symptoms will be assessed at baseline (T0), after 2 weeks (T1), and after 4 weeks (T2). According to the literature, intraclass correlation coefficient (ICC) will be used to assess the consistency of the assessors (33). The ICC values among assessors were 0.912, indicating the consistency was good. The procedure for the site visit is detailed in **Table 3**.

**Table 3 T3:** Time schedule of screening, interventions and assessments.

	Recruitment	Baseline	Assessments	
			After 2 weeks	After 4 weeks
Time point		T0	T1	T2
Prescreening for eligibility, consenting and clinical interview				
Recruitment				
Eligibility screening	✓			
Informed consent	✓			
Allocation	✓			
Primary outcome assessment				
MCCB		✓	✓	✓
Second outcome assessment				
BPRS		✓	✓	✓
PANSS		✓	✓	✓
CGI		✓	✓	✓
SQLS		✓	✓	✓
SDSS		✓	✓	✓
fNIRS		✓	✓	✓
GIQ		✓		
**Safety**				
ARS			✓	✓

A checkmark (√) indicates the time point at which each assessment is carried out. ARS, Adverse Reaction Scale; BPRS, Brief Psychiatric Rating Scale; CGI, Clinical Global Impressions; fNIRS, Functional Near-Infrared Spectroscopy; GIQ, General Information Questionnaire; MCCB, MATRICS Consensus Cognitive Battery; PANSS, Positive and Negative Syndrome Scale; SDSS, Social Dysfunction Screening Scale; SQLS, Schizophrenia Quality of Life Scale.

The primary outcome measure is the change in the MCCB. It covers a total of seven different cognitive domains, including speed of processing, attention/vigilance, working memory, verbal learning, social cognition, reasoning and problem-solving (31). The MCCB is the gold standard measure of cognition in schizophrenia in clinical trials (34). It includes (1) Trail Making A Test, (2) Symbol Coding, (3) Hopkins Verbal Learning Test-Revised, (4) Digit Span Test, (5) Stroop Color-Word Test, (6) Spatial Span Test, (7) VFT, (8) Mazes, (9) Brief Visuospatial Memory Test-Revised, and (10) Continuous Performance Test-Identical Pairs.

The second outcome measures include the changes in general information questionnaire, Clinical Global Impressions (CGI) Scale, Brief Psychiatric Rating Scale (BPRS), Positive and Negative Syndrome Scale (PANSS), and fNIRS. Specifically, Clinical Global Impressions (CGI) is employed to evaluate both the severity of a patient’s condition and the efficacy of treatment. It comprises three components: the clinical global impressions-severity, which assesses the severity of illness; the clinical global impressions-improvement, which evaluates global impressions of improvement; and the efficacy index, which measures the overall efficacy of the treatment. BPRS is utilized to assess the severity of psychotic symptoms in patients, with higher scores indicative of more severe symptoms. PANSS includes a positive symptom scale and a negative symptom scale, each containing 7 items, as well as a general psychopathology scale with 16 items, culminating in a total of 30 items. Additionally, it incorporates 3 supplementary items designed to evaluate the risk of aggression. Each item on the PANSS has a definition and a specific 7-point operational rating scale. Both PANSS and BPRS will be used to assess psychotic symptoms from different perspectives (35, 36). By combining these two scales, we can more comprehensively capture changes in patients’ symptoms, thereby more accurately evaluating the effects of the treatment. The Social Dysfunction Screening Scale (SDSS) and Schizophrenia Quality of Life Scale (SQLS) is utilized to assess patient’s social function and quality of life, respectively.

A 48-channel fNIRS system (NirScan, Danyang Huichuang Medical Equipment Co. Ltd, China) will be employed in this study. The Chinese version of the VFT will be used to evaluate verbal fluency, working memory, verbal recall, attention, and retrieval (37). The VFT paradigm comprises a 30-second pre-task baseline period, a 60-second task period, and a 70-second post-task baseline period. During pre-task and post-task baseline periods, participants will be instructed to repeatedly count numbers from one to five. In the task period, subjects will be asked to verbally generate as many phrases as possible using three Chinese characters. A total of fifteen light source probes and sixteen light detector probes will be positioned on the bilateral frontotemporal cortex, ensuring a 3.0 cm distance between each light source and detector probe. In accordance with the 10/20 electrode placement system, the central probe will be aligned with FPz, while the lower boundary of the probe array will be extended from Fp1 to Fp2. Measurements of oxyhemoglobin, deoxyhemoglobin, and total hemoglobin will be conducted to assess hemodynamic changes. Raw fNIRS data will be preprocessed using the MATLAB toolkit Home 3. Five statistical measures of change in oxy-Hb signals, including mean, variance, skewness, kurtosis, and peak value will be calculated using the spatial average for all 48 channels. This yielded a total of 240 independent features for each subject.

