## Background

Schizophrenia is a severe and chronic psychiatric disorder with a lifetime prevalence of approximately 1% (1). It is characterized by positive symptoms, negative symptoms, and cognitive impairments such as deficits in working memory, verbal learning, attention, processing speed, and social cognition (2, 3). As a core symptom of schizophrenia, cognitive impairments typically manifest early in the disease course and may persist, significantly impacting patients’ social functioning and daily living abilities (4, 5). These cognitive impairments associated with schizophrenia (CIAS) encompass deficits in working memory, verbal learning, attention, processing speed, and social cognition (4, 5). Deficits in working memory and executive functions can hinder patients’ ability to plan, organize, and complete tasks, while impairments in social cognition may lead to difficulties in interpersonal relationships (6–8). Despite adequate pharmacological treatment, approximately 30% of individuals with schizophrenia persist in exhibiting cognitive impairments. Additionally, pharmacological treatments are often associated with substantial financial burdens for families, low compliance, and potential adverse effects, including extrapyramidal symptoms, endocrine, and metabolic disturbances (6). Consequently, the development of effective non-pharmacological alternatives for cognitive impairments is a major research priority.

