### Statistical methods

The Shapiro-Wilk Test will be used to analyze whether the data conform to normality. If the quantitative data conform to a normal distribution, they will be expressed as the mean and standard deviation (SD); if they do not, they will be displayed as median values and interquartile range (IQR). Categorical data will be presented as counts with percentages. To evaluate differences in baseline characteristics between groups, t-tests, nonparametric tests, chi-square tests, Mann-Whitney U tests, and ANOVA will be employed appropriately. The Fisher exact test or χ² test will be used to compare adverse effects between groups.

In accordance with the CONSORT guidelines, analyses will be conducted following the intention-to-treat (ITT) principle, whereby all participants will be analyzed as originally randomized. A line graph will be utilized to depict values across different time points. To evaluate between-group and within-group differences over time for both primary and secondary outcomes, we will appropriately apply generalized linear mixed models and repeated measures ANOVA. A stepwise model selection process will be utilized to identify a parsimonious multivariable regression model. Age, gender and DDD doses of antipsychotic medications will be included as covariates in all models. The likelihood ratio test (LRT) will be utilized to assess the treatment effect by determining whether the coefficients for both the treatment and the interaction between time and treatment in the model are equal to zero. To account for multiple comparisons across multiple time points, p-values will be adjusted using the Bonferroni correction method. All statistical analyses will be conducted using SPSS 20.0. P < 0.05 is considered to be a statistically significant difference.

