### Harms

To assess the safety and potential adverse effects of tDCS, this study will systematically analyze both serious and non-serious adverse events. Following each tDCS session, all participants will be required to complete the tDCS Adverse Events Questionnaire. Commonly reported side effects include sensations of tingling, mild erythema, itching, and discomfort at the site of stimulation. Participants will evaluate their adverse experiences on a scale ranging from 0 to 5. All adverse events will be recorded in the case report form (CRF). The tDCS device will be administered by a therapist with specialized training and experience in its application. Consequently, it is anticipated that participants will not encounter any significant health risks or adverse events. In the event that a serious adverse event does occur, the participant will be withdrawn from the trial, and the incident will be reported to the ethics committee.

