As a non-pharmacological intervention, the combination of tDCS and MT can serve as a valuable adjunct to traditional antipsychotic medications. First, patients with schizophrenia often require long-term use of antipsychotic medications, which may lead to side effects such as extrapyramidal symptoms, endocrine disturbances, and metabolic issues. As non-pharmacological interventions, tDCS and MT may help mitigate these adverse effects, thereby improving patients’ overall quality of life. Second, the accessibility of tDCS and MT makes this combination a promising option for widespread clinical use. tDCS devices are relatively portable and easy to operate, and MT is simple to implement. If future research confirms the efficacy of this intervention, it could be widely adopted in various settings, including community health centers, rehabilitation facilities, and even home-based care. Third, the cost-effectiveness of tDCS and MT makes this combination a promising option for widespread clinical use. Future research should focus on identifying the optimal parameters for tDCS and MT, as well as developing standardized protocols for their use in clinical practice.

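### The Adverse Reaction Scale has no baseline rating, so if it covers symptoms that antipsychotics also cause, complaints present at entry cannot be told from new ones

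*Protocol article*

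**What the plan says.** In the Outcomes section, Table 3 has one row under Safety, the ARS, with ticks after 2 weeks (T1) and after 4 weeks (T2) and none at baseline (T0). The legend explains what a tick means: "A checkmark (√) indicates the time point at which each assessment is carried out. ARS, Adverse Reaction Scale". The MCCB, BPRS, PANSS, CGI, SQLS, SDSS and fNIRS rows are ticked at all three time points. The general information questionnaire is ticked at T0 only.

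Statistical methods gives the analysis: "The Fisher exact test or χ² test will be used to compare adverse effects between groups". The article mentions no baseline adjustment for this comparison.

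The Harms section states the aim: "To assess the safety and potential adverse effects of tDCS, this study will systematically analyze both serious and non-serious adverse events". It describes a separately named instrument: "Following each tDCS session, all participants will be required to complete the tDCS Adverse Events Questionnaire". The effects it names are local: "Commonly reported side effects include sensations of tingling, mild erythema, itching, and discomfort at the site of stimulation".

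Table 1 requires current treatment with an atypical antipsychotic. The Background section acknowledges that drug treatment carries "potential adverse effects, including extrapyramidal symptoms, endocrine, and metabolic disturbances". There is a concurrent arm without either study intervention: "Participants in the control group (Group 5) will continue their regular medication treatment without receiving tDCS or MT".

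**The concern.** Every participant arrives on an antipsychotic at a stable dose, and the article itself says that such drugs have side effects. A complaint that existed before the first session may well still be there at T1 and T2. Without a T0 rating, nothing on the ARS shows whether it is old or new.

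Two things would be at stake. The adverse-effect rate reported for each arm would include background complaints and so overstate what arose during treatment. The contrast between an active arm and a control arm would also shrink, because patients already affected count as events in both arms. With 12 patients per arm there is little room for that loss.

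This belongs to the protocol and not to a later analysis plan. A plan can define a treatment-emergent event, but it cannot recover a baseline value that was never collected.

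**Working it through.** **Inputs from the protocol article.** 12 patients per arm (Sample size calculation: 45 / (1 − 0.20) = 56.25, so 57, raised to 60 = 5 × 12). Fisher's exact or χ² test between groups, with P < 0.05 (Statistical methods). ARS at T1 and T2 only (Table 3). The article gives no adverse-effect rate, so there is no safety figure of its own to reproduce.

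**Assumptions.** The ARS includes symptoms that antipsychotics also cause. A proportion p0 of patients in each arm has such a symptom at entry and still has it when rated; p0 is varied from 0 to 0.6. A new effect arises in 50% of the unaffected active-arm patients and in no controls. All 12 patients per arm are rated.

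**Step 1: what is observed without T0.**

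Control arm rate = p0. Active arm rate = p0 + 0.5 × (1 − p0). Visible risk difference = 0.5 × (1 − p0).

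At p0 = 0.3: control 0.30, active 0.30 + 0.5 × 0.70 = 0.65, difference 0.35. At p0 = 0.6: control 0.60, active 0.60 + 0.5 × 0.40 = 0.80, difference 0.20.

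**Step 2: type I error and power.** Every possible 12 v 12 table was enumerated, and the binomial probabilities of the tables with two-sided Fisher p < 0.05 were summed. Type I error uses rate p0 in both arms; power uses the two rates from step 1.

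| p0 | Expected pre-existing per arm (12 × p0) | Type I error | Visible risk difference | Power |
|---|---|---|---|---|
| 0 | 0 | 0.000 | 0.50 | 0.81 |
| 0.1 | 1.2 | 0.002 | 0.45 | 0.53 |
| 0.2 | 2.4 | 0.012 | 0.40 | 0.39 |
| 0.3 | 3.6 | 0.017 | 0.35 | 0.29 |
| 0.4 | 4.8 | 0.021 | 0.30 | 0.21 |
| 0.5 | 6.0 | 0.023 | 0.25 | 0.14 |
| 0.6 | 7.2 | 0.021 | 0.20 | 0.09 |

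**Step 3: how much a T0 rating recovers.** With no events in controls, Fisher's test needs at least 5 of 12 in the active arm (5 v 0 gives p = 0.037; 4 v 0 gives p = 0.093).

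- If effects new or worse than at T0 are compared, and affected patients worsen at the same assumed 50%, the rates are 0.50 v 0 and power is P(X ≥ 5), X ~ Bin(12, 0.50), = 0.81.
- If affected patients can never register a worsening, the active rate over all 12 is 0.5 × (1 − p0). At p0 = 0.3, power is P(X ≥ 5), X ~ Bin(12, 0.35), = 1 − 0.583 = 0.42. At p0 = 0.6 it is P(X ≥ 5), X ~ Bin(12, 0.20), = 1 − 0.927 = 0.07, which is no gain.

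In both cases the T0 rating takes the background out of the arm rates: under these assumptions the control rate returns from p0 to 0, and the risk among patients unaffected at entry can be read directly as 0.50. How much power returns depends on whether the scale can record worsening.

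**The case against.** The strongest reply is that nothing shows the ARS to cover antipsychotic effects. The article gives no items, scoring, recall period or attribution rule for it. Harms frames safety around tDCS and names reactions where the electrode sits, which cannot exist before the first session. If the ARS records only those, a blank T0 cell is the natural schedule. This stands, and it is why the point is conditional. It does not settle the matter, because Harms describes a differently named questionnaire tied to tDCS sessions. Groups 4 and 5 have no such sessions, so the ARS is the only scheduled safety measure that clearly applies to all five arms.

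The second reply is that randomization, unchanged drug doses and a medication-only arm make background complaints equally likely in every arm. This also stands as far as it goes: no arm is favoured in expectation, and type I error stays well below 0.05. It does not protect the within-arm rates or the power.

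Stronger readings are tempting, and the document does not support them:
- A reader might infer that antipsychotic side effects are counted as effects of the study arm. No section states such a rule.
- A reader might infer that chance imbalance between small arms swamps any signal. Gaps of 3 or 4 patients between two arms of 12 do occur by chance, but a gap of 4 never reaches p < 0.05 on Fisher's test; the smallest p-value is 0.093 (4 v 0).
- The Discussion says that "tDCS and MT may help mitigate these adverse effects", and a reader might conclude that the trial must be able to test this. It is a remark about possible benefit; none of the three objectives in the Background section concerns drug side effects.

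**Conclusion.** The missing T0 rating is a fact of Table 3, and its consequence is conditional. If the ARS includes symptoms that antipsychotics also cause, within-arm adverse-effect rates will contain pre-existing complaints and true differences between arms will be diluted. The between-group test remains valid, so the cost is a real effect overlooked and not a false one declared. Under the assumed 50% new-effect rate, power at 12 v 12 falls from 0.81 to 0.29 at 30% background prevalence and to 0.09 at 60%. These rates are illustrative, since the article supplies none. If the scale covers only local stimulation reactions, the loss is nil. The severity is minor: the main cognitive outcome is untouched and the remedy is cheap.

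**What to change.** Add an ARS tick at T0 in Table 3, with the rating done before the first session. State that the between-group comparison uses effects that are new or worse than at T0. One sentence on what the ARS covers, and how it relates to the tDCS questionnaire described in Harms, would reconcile the two places and show whether the concern applies at all.

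The cost is a few minutes per patient at a visit already scheduled, plus one line of event definition. Recruitment began in December 2024, so patients already treated will have no T0 value. Report how many there are, and show their events separately from those with a baseline.

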### Sample size calculation

The sample size was calculated using G*Power software (G*Power, Version 3.1.9.7) based on a previous study (38). The study parameters include a Type I error rate of 0.05, a statistical power of 80%, and an effect size of 0.25. Based on these calculations, the required sample size was determined to be 45 participants using a repeated measures analysis of variance (ANOVA) model. Accounting for an estimated 20% dropout rate, a target sample size of 60 patients (12 per group) was established. Consistent with the previous literature by Emuk et al. (39), they also planned to include 12 participants per group, for a total of 60 participants. Here are the main reasons: When designing a pilot investigation where there is no prior information upon which to base the sample size, the recommendation would be a sample size of 12 per group as being appropriate. Three reasons for justifying a sample size of 12 per group will be given based on feasibility, gains in the precision about the mean and variance, and regulatory considerations (40). This sample size is expected to provide adequate statistical power to address the study objectives.

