This study protocol proposes a non-pharmacological approach by integrating tDCS with MT to investigate their synergistic effects on cognitive impairments in individuals with schizophrenia.This proof-of-concept study has three overall objectives. The first objective is to assess the efficacy of tDCS combined with MT on the treatment of cognitive impairments in patients with schizophrenia. We hypothesize that the integration of tDCS with MT will demonstrate greater effectiveness in ameliorating cognitive impairments compared to the application of either MT or tDCS. The second objective is to evaluate the efficacy of this integrated treatment approach on the positive and negative symptoms, as well as the quality of life, and social functioning. We expect that tDCS combined with MT will ameliorate both positive and negative symptoms and enhance overall functioning. The third objective is to investigate hemodynamic changes in the brain and explore the neural mechanisms involved in this combined treatment process by utilizing fNIRS during verbal fluency tasks (VFT). We propose the hypothesis that combined treatment will ameliorate prefrontal dysfunction, as measured by fNIRS, with more pronounced improvements observed in the combined group compared to those receiving tDCS or MT alone.

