## Method

### Study design

This is a prospective, single-center, randomized, double-blind, sham-controlled study designed to assess the effects of tDCS combined with MT on the improvement of cognitive functions in patients with schizophrenia. Eligible participants will be recruited and randomly allocated into five groups in equal proportions (1:1:1:1:1): active tDCS combined with MT group (Group 1), sham tDCS combined with MT group (Group 2), active tDCS group (Group 3), MT group (Group 4), and control group (Group 5). Assessments will be conducted at baseline (T0), after 2 weeks (T1), and after 4 weeks (T2). The study design is depicted in **Figure 1**.

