Despite its advantages, this study has several limitations. Firstly, the relatively small sample size within each group may reduce the statistical power and limit the generalizability of the results. Secondly, this research will be conducted at a single site, which affects the external validity of the findings. Thirdly, the long-term effects and sustainability of the experimental treatment have not been comprehensively evaluated. Although the treatment period lasts for up to 4 weeks, the assessment of the long-term therapeutic effects after the treatment ends has not been conducted, which takes into account the limitation of the length of hospital stay. Therefore, the combined strategy warrants validation through larger, prospective multicenter studies to further investigate its long-term therapeutic effects on cognitive impairments in schizophrenia.

This randomized, double-blind, sham-controlled clinical study aims to demonstrate the synergistic effect of tDCS and MT on cognitive impairments, psychotic symptoms, and overall functioning in individuals with schizophrenia. Findings from this study may elucidate the potential mechanisms underlying the combined treatment on cognitive impairments and identify a novel target for schizophrenia. Given that the majority of schizophrenia patients experience a significant burden from pharmacological treatments, the implementation of non-pharmaceutical treatments holds considerable importance for both patients and clinical psychiatrists.

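### The 80% power fits the omnibus five-group by three-visit test; power for the hypothesised contrasts (combination versus tDCS alone and versus MT alone) is unstated and reaches 80% only at about 1.2 to 1.4 SD of change

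*Protocol article*

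**What the plan says.** The section Sample size calculation gives the inputs: "The study parameters include a Type I error rate of 0.05, a statistical power of 80%, and an effect size of 0.25". It then reports that "the required sample size was determined to be 45 participants using a repeated measures analysis of variance (ANOVA) model". With 20% dropout the target becomes 60, or 12 per group. The section does not say which ANOVA effect was powered, which correlation between visits was used, or which effect-size convention applies. It adds a rule of thumb of 12 per group for pilot work and closes with "This sample size is expected to provide adequate statistical power to address the study objectives".

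The first objective, at the end of the Background, carries the main hypothesis: the combination will show "greater effectiveness in ameliorating cognitive impairments compared to the application of either MT or tDCS". The Discussion repeats it. The limitations paragraph of the Discussion says that "the relatively small sample size within each group may reduce the statistical power and limit the generalizability of the results".

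Under Statistical methods, the treatment effect is tested by a likelihood ratio test on the treatment and time-by-treatment coefficients together.

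**The concern.** An omnibus interaction test asks whether any of five trajectories differs from any other. It can be significant because the untreated control group lags behind, with no difference between the combination and either single therapy. Power for that test is not power for the two hypothesised contrasts, each of which has 12 patients per arm before dropout.

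If the adequacy sentence stands, a non-significant contrast between the combination and a single therapy may be read as evidence from a trial with 80% power for that question. A significant one, in a comparison with low power, would tend to overstate the effect. The Discussion looks ahead to a therapeutic strategy if the hypothesis is validated, so the reading of these contrasts matters.

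**Working it through.** **Inputs from the article.** Alpha 0.05; power 80%; effect size 0.25 (read as Cohen's f, the G*Power metric for ANOVA); k = 5 equal groups; m = 3 visits; N = 45, then 60 with 20% dropout. **Assumed, not stated:** visit correlation ρ = 0.5, sphericity (ε = 1), two-sided pairwise tests.

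**1. Reproducing 45.** For the within-between interaction, λ = f²·N·m/(1−ρ), df1 = (k−1)(m−1), df2 = (N−k)(m−1).
- N = 45: λ = 0.0625 × 45 × 3/0.5 = 16.9; df 8 and 80; power 0.810.
- N = 40: λ = 15.0; df 8 and 70; power 0.745.

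So 45 is the smallest equal-group total that reaches 80%. Dropout: 45/0.8 = 56.25, so 57, and 60 for equal groups. The stated arithmetic is sound.

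The result depends on the unstated inputs in both directions. At N = 45, power is 0.64 with ρ = 0.3, 0.97 with ρ = 0.7, and 0.71 with ε = 0.75.

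**2. Detectable difference for one contrast.** Two-sample t test, noncentrality d·√(n/2), df = 2n−2, with d in SD of change.

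| n per arm | d for 80% power | power at d = 0.5 |
|---|---|---|
| 12 (all randomised) | 1.20 | 22% |
| 9.6 (60 less 20%, over 5) | 1.36 | 18% |
| 9 (the calculated 45, over 5) | 1.41 | 17% |

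**3. Pairwise power under the article's own f = 0.25.** Let the combination's gain over control be D, building linearly over the three visits (time scores 0, 0.5, 1; sum of squares about their mean 0.5). Let each group gain a fraction g of D. Then f² = D²·Σ(g−ḡ)²·0.5/(5 × 3), so D = √(0.9375/(0.5·Σ(g−ḡ)²)). At ρ = 0.5 the SD of change, σ√(2(1−ρ)), equals σ. All three groups other than the combination and control (sham tDCS plus MT, tDCS alone, MT alone) take the same fraction.

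| Pattern | Σ(g−ḡ)² | D | Combination minus single therapy | Power, 9 to 12 per arm |
|---|---|---|---|---|
| Only the combination works | 0.800 | 1.53 | 1.53 SD | 86–95% |
| Single therapies give half | 0.500 | 1.94 | 0.97 SD | 49–62% |
| Single therapies give three quarters | 0.575 | 1.81 | 0.45 SD | 15–19% |

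**4. Dependence on the SD scale.** A difference of 0.5 SD in raw score units is 0.5/√(2(1−ρ)) in SD of change: 0.65 at ρ = 0.7 and 0.91 at ρ = 0.85. Change-score power is then 33–57% at 12 per arm and 25–44% at 9 per arm.

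**5. Precision.** The 95% confidence interval half-width is t(0.975)·√(2/n). With 12 per arm it is 0.82 SD (variance pooled over five groups) to 0.85 SD (two arms only). After dropout it is 0.92 to 1.0 SD over 9.6 to 9 per arm.

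**The case against.** The strongest defence is that the sizing broadly matches the planned analysis. The treatment test under Statistical methods is itself omnibus, the arithmetic reproduces, and the dropout step is right. The study calls itself proof-of-concept, the limitations paragraph warns about power, and the Discussion asks for larger multicentre validation. All of this stands, and it lowers the severity. It does not supply power for the contrasts in the hypothesis, and the adequacy sentence refers to the study objectives without restriction.

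Four stronger readings are tempting but not supported:
- **Pairwise power is about 20%.** That holds for d = 0.5 on the SD of change, which is my illustration and not an input of the article. Its own f = 0.25 gives anything from 15% to 95% across the patterns above, and a higher visit correlation raises power for a given raw difference.
- **The power claim is false.** It is not shown for the contrasts. If neither single therapy worked, f = 0.25 would give more than 80%.
- **The article admits low power.** It says only that small groups may reduce power.
- **The article says it had no prior data while citing a previous study.** The remark about lacking prior information sits inside a general rule for pilot studies. It is awkward beside the cited study, but it is not a statement about this trial.

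**Conclusion.** The point holds as a mismatch between the test that was powered and the hypotheses that are stated. The 80% is reproduced by the omnibus interaction; no power is given for the combination against tDCS alone or against MT alone. Of the three patterns examined under f = 0.25, only the one in which neither single therapy works gives 80% or more. The Background argues against that pattern, since it reports cognitive benefit from each therapy alone. The half-benefit pattern is closer to that rationale and gives 49–62%.

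This rests on reading 0.25 as Cohen's f, on an interaction test with ρ = 0.5 and sphericity (inferred from the exact match at 45), and on two-sided tests of change at 0.05 without adjustment for the two contrasts. It should be fixed, but it does not threaten the conduct of the trial.

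**What to change.** Keep 60 patients and revise the section Sample size calculation:
- State that the 80% applies to the omnibus group-by-time test, and give the correlation, the sphericity assumption and the effect-size convention.
- State that each contrast of the combination with a single therapy has 80% power only for a difference of about 1.2 SD of change, or about 1.4 SD after dropout.
- Delete the adequacy sentence, or limit it to the omnibus test, so that it agrees with the limitations paragraph.
- Report the two contrasts as estimates with 95% confidence intervals, state the expected half-width (about 0.82 to 0.85 SD at 12 per arm, 0.92 to 1.0 SD after dropout), and read them as proof-of-concept.

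The cost is wording and a less favourable power statement. No extra patients are needed.
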